### Study schedule

During the screening visit, detailed study information is provided to participants (see Additional file 1) and written informed consent obtained (see Additional file 2). A member of the research team assesses symptoms severity and participant’s eligibility and measures vital signs. Following a blood test, participants are allocated into the ‘Depression with inflammation’ or ‘Depression without inflammation’ strata of the study. Study participants are taken off their regular antidepressant medication after screening and in the week before trial medication is started.

During the baseline visit, demographics (including date of birth, sex and race) and years of education are recorded. In addition, psychiatric and medical history, number of psychotropic medications received, alcohol and nicotine history, vital signs and anthropometric data are collected. A physical examination is also performed during this visit.

According to stratified recruitment into the two treatment strata and the random allocation into two treatment groups, participants in both the ‘Depression with inflammation’ and ‘Depression without inflammation’ stratum receive celecoxib 400 mg daily or placebo. The starting dose of vortioxetine in both study strata is vortioxetine 5 mg daily for those receiving celecoxib, due to possible drug–drug interactions, and vortioxetine 10 mg daily for those receiving placebo. Two weeks after commencement of treatment, participants receiving vortioxetine 5 mg daily and 10 mg daily are provided the opportunity to increase to vortioxetine 10 mg or 20 mg daily, respectively, following an assessment by a research clinician (Fig. 2). The decision to increase the dose or to leave it the same is made by the trial psychiatrist after review of the change in depressive symptoms from baseline according to the MADRS and the presence and severity of side effects, rated by a blinded researcher. The dose of vortioxetine is increased only if the side effects experienced are easily manageable and the participants have not achieved recovery (MADRS score < 7). In study participants reporting symptoms consistent with an excessive plasma concentration of vortioxetine, the trial psychiatrist will reduce the dose of vortioxetine without informing the participant or blinded researchers administering scales. After six weeks of treatment, celecoxib and placebo are ceased, but the antidepressant vortioxetine is continued for at least two weeks. After the completion of the RCT phase, study participants are given the opportunity to continue taking vortioxetine into the post-RCT study phase for up to six months. Following an assessment by a research clinician, study participants who had been taking vortioxetine 5 mg or 10 mg daily during the RCT due to celecoxib co-administration are given the opportunity to increase to vortioxetine 10 mg and 20 mg daily, respectively; otherwise vortioxetine is continued in the post-RCT phase at the same dose as for the RCT phase.

A member of the research team assesses symptoms severity, cognitive function, functional and workplace productivity, and other secondary assessments at baseline visit, fortnightly during the RCT period, and at the three-month and six-month post-RCT visits (see Fig. 1). Participants are asked to report any treatment side effects at each visit. They are also asked to return the vortioxetine packages at each fortnightly visit and receive new ones regardless of whether they have finished a packet or not, so that compliance can be gauged. Similarly, the celecoxib or placebo medication is also returned at the end of six weeks.

An additional checklist and an additional figure have been provided for further details regarding the study of enrolment, interventions and assessments for the current study (Additional file 3 and Fig. 3).

**Fig. 3 Fig3:**
[figure not shown]
SPIRIT figure. Schedule of enrolment, interventions and assessments

### Inclusion and exclusion criteria

Participants with MDD are selected according to the following selection criteria: they must be aged 18–75 years; be outpatients in a psychiatric setting with MADRS score ≥ 26 at screening and baseline visits; have at least one prior episode of depression, validated by previous treatment; and the current major depressive episode (MDE) is confirmed by the MINI and has a duration of at least three months. Exclusion criteria are: current alcohol and/or substance use disorder; presence of a co-morbid psychiatric disorder as a focus of clinical concern; primary inflammatory or immune-related disorder; neurodegenerative disorder; history of neurological disorder; past peptic ulcer disease or history of gastrointestinal (GI) bleeding; unstable coronary artery or cardiovascular disease; renal impairment; physical, cognitive, reading, and learning or language impairment. In addition, past hypersensitivity to vortioxetine or to celecoxib and use of concomitant medications able to affect cognitive function or to induce drug–drug interaction are also considered exclusion criteria.

### Data storage and participant confidentiality

Data are stored both on secure, password-protected internal servers and also physically in locked storage space in locked rooms, accessible only to researchers on the trial individually approved by the Ethics Committee mentioned below. Biological specimens are marked with a code unidentifiable to persons unaffiliated with the project. Prepared data reports may be shared with future collaborators but do not contain identifiable participant information. Data will be stored for 15 years after study completion. The results of the trial will be made publicly available via official publication and media release at the trial’s conclusion.

An independent Data Monitoring Committee (DMC) will be formed and comprise experienced local, national and international members.

### Ethics

The study was approved by the Royal Adelaide Hospital Human Research Ethics Committee (HREC; reference number R20170320 HREC/17/RAH/111). Study participants have all study details explained to them in writing and in person by a member of the study team before giving written informed consent. The consent form states that refusal to participate or subsequent withdrawal from the study will in no way influence any treatment that the participant would receive, at the time of the study or in the future. Any and all serious adverse events to occur considered to be related to the trial are reported to the aforementioned HREC by the PI. In the event of participants suffering harm due to the study, the trial is covered by indemnity insurance.

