Secondary hypothesis	A larger reduction of circulating levels of the inflammatory marker CRP will be observed in the group of depressed patients who are treated with antidepressant plus anti-inflammatory medication	A larger reduction of circulating levels of the inflammatory marker CRP will be observed in the group of depressed patients who are treated with vortioxetine plus celecoxib 400 mg
Secondary objective 2	To test whether there is evidence of a different effect of the combined treatment in the two inflammation strata	To test whether there is evidence of a different effect of the combined treatment with vortioxetine and celecoxib 400 mg in the two inflammation strata
Secondary objective 3	To investigate the safety of the anti-inflammatory treatment when combined with antidepressant	To investigate the safety celecoxib 400 mg treatment when combined with vortioxetine
Secondary objective 4	To investigate the effects of the antidepressant on cognition, psychosocial and workplace performance measures in MDD	To investigate the effects of vortioxetine on cognition, psychosocial and workplace performance measures in MDD

The secondary objectives of the study are:To investigate the anti-inflammatory effects of a combined treatment of MDD with vortioxetine and celecoxib in individuals with baseline inflammation (CRP levels > 3 mg/L) over a six-week period. We aim to demonstrate a larger reduction of circulating levels of the inflammatory marker CRP in the group of depressed patients who are treated with antidepressant plus anti-inflammatory medication (see Table 1).To test whether there is evidence of a different effect of the combined treatment in the two inflammation strata, although the study is not powered to detect this effect (see Table 1).To investigate the safety of the anti-inflammatory treatment of celecoxib 400 mg when combined with vortioxetine (see Table 1).To investigate the effects of vortioxetine on cognition (using the THINC-It tool) and on psychosocial and workplace performance measures in MDD (see Table 1).

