**Fig. 1 Fig1:**
[figure not shown]
Clinical timeline of the trial. Participants will complete assessment sessions fortnightly over the 8-week RCT period. “R” circles represent 1:1 random assignment of participants within each study stratum

The principal investigator (PI) and trial psychiatrist are aware which study participants are receiving celecoxib and which participants are receiving placebo, so that the dose of vortioxetine can be determined. An approximately twofold increase in vortioxetine plasma concentration has been observed following co-administration of bupropion, a strong CYP2D6 inhibitor [43]. When bupropion was added to vortioxetine 10 mg daily at steady state, a higher incidence of adverse events was observed than when vortioxetine was added to bupropion at steady state. This may be explained by pharmacodynamics or combined pharmacodynamic/pharmacokinetic effects following CYP2D6 inhibition with bupropion, which seem to be more pronounced when the inhibition is initiated when vortioxetine is in steady state than before vortioxetine is administered [43]. In the study where bupropion was added to vortioxetine, increased incidences of nausea, headache and vomiting were noted [43]. As celecoxib is also a strong inhibitor of CYP2D6, individuals receiving celecoxib start at a lower dose of vortioxetine, 5 mg daily, and are restricted to a maximum dose of 10 mg daily for the duration of co-administration. This is consistent with guidelines recommending the dose of vortioxetine be reduced by half if a strong CYP2D6 inhibitor is co-administered (Trintellix Product Monograph. Page 1 of 44, Lundbeck).

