### Double-blinding

The trial psychiatrist and the study PI do not administer the MADRS or any of the functional rating scales, as they are aware of both the dose of vortioxetine and whether a participant is receiving celecoxib or placebo. While the PI is aware which study participants are receiving celecoxib and which participants are receiving placebo, the study rater and participants remain fully blinded during the entire trial. Celecoxib has been encapsulated to have the same appearance as placebo; celecoxib and placebo have been packaged in the same way. A randomisation list has been created by the Royal Adelaide Hospital pharmacy and provided to the trial psychiatrist. The dosage of vortioxetine is not marked specifically on the package provided to participants in order to maintain blinding of participants as well as researchers administering the scales who may see the boxes.

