## Trial status

The trial has commenced recruitment and participant inclusion in November 2017.

If any important changes to the study protocol become necessary, where appropriate, the PI will notify the HREC, trial register, financial sponsor, University and the present journal. The HREC and PI, respectively, have the power to end the study early if the need arises. The trial is subject to audit at any time by the HREC and/or DMC.

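### Serious adverse events reach the ethics committee only if someone attributes them to the trial, and visit collection asks only for treatment side effects; at the ethics step the attribution may be made with knowledge of the arm

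*Protocol article*

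**What the plan says.** The reporting rule is in the Ethics section of the protocol article: "Any and all serious adverse events to occur considered to be related to the trial are reported to the aforementioned HREC by the PI". The rule does not say who decides whether an event is related.

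On who knows the allocation, the Recruitment and study design section says: "The principal investigator (PI) and trial psychiatrist are aware which study participants are receiving celecoxib and which participants are receiving placebo". The Double-blinding section repeats this for the PI and adds that "the study rater and participants remain fully blinded during the entire trial".

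On collection, the Study schedule section says: "Participants are asked to report any treatment side effects at each visit". The same section has a blinded researcher rate the presence and severity of side effects, and mentions this as an input to the vortioxetine dose decision. The Discussion describes the safety assessment in the same terms, as the measurement of side effects at each visit.

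On analysis, the Results analysis section plans a descriptive summary of adverse events and of the suicide severity scale. It does not limit that summary to related or serious events.

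**The concern.** One secondary objective is "To investigate the safety of the anti-inflammatory treatment of celecoxib 400 mg when combined with vortioxetine". For that purpose, and for ethics oversight, the useful raw material is every untoward event, with causality as a later and separate judgement. Here attribution comes first, at two points. The ethics committee is told only of serious events that someone has linked to the trial, and participants are prompted only for events that they themselves link to treatment.

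The ethics step has a further weakness. The article gives an assessor who knows the arm reasons to expect certain events on celecoxib: the Blood analysis section cites a higher risk of gastrointestinal bleeding with anti-inflammatory medication, and the Recruitment and study design section expects a drug interaction with vortioxetine. If relatedness were judged with that knowledge, the same event could be notified in one arm and not in the other. At stake are how complete a picture the ethics committee has while the trial runs, and how complete the adverse event record is at the end.

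**Working it through.** The article gives no serious event rate and no figure for how often events are judged related, so no arithmetic applies. The check sets the three relevant steps side by side and follows one event through them.

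| Step (section) | Which events pass | Who applies the filter | Does that person know the arm? |
|---|---|---|---|
| Visit collection (Study schedule) | Side effects of treatment | The participant, by what he or she reports | No |
| Notification to the HREC (Ethics) | Serious events held to be trial-related | Not stated; the PI is named as reporter | The reporter does; whoever decides relatedness is not identified |
| Safety summary (Results analysis) | Adverse events, with no relatedness limit | None stated | Not applicable |

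1. **Notification.** The restriction is written into the rule. This is a stated limit, not a detail left out of a condensed article. A serious event held to be unrelated has no stated path to the HREC.

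2. **Knowledge of the arm.** The reporter is unblinded. That the PI also makes the relatedness judgement is an inference, because the rule is in the passive voice. What can be said is that nothing in the rule keeps the judgement blinded. Elsewhere the protocol takes care on this point: the Double-blinding section keeps the PI and the trial psychiatrist away from the MADRS and the functional scales precisely because they know the dose and the allocation.

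3. **Collection.** The visit question is attributional too, but participants are blinded. Its consequence is possible under-recording, not a difference between arms caused by knowledge of the allocation.

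4. **Summary.** The planned summary has no relatedness limit, but it can only contain what was recorded. The article moves from side effects at collection to adverse events at analysis without linking the two terms.

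5. **One event traced.** Take a serious event that the participant does not see as a side effect and that is held to be unrelated. At the visit, the question as worded does not ask for it. Under the Ethics rule, it is not reported. The summary would include it if it were on file, but no stated step puts it there. Suicidal ideation and behaviour are better covered, because they have their own clinician-rated scale that does not depend on attribution.

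**The case against.** The strongest reply is that the Ethics rule governs notification to a committee and does not define the safety data set. That is correct, and it limits the point. A reader might infer that the safety objective itself rests on an unblinded filter. The documents do not support this: safety is assessed from side effects reported at each visit by blinded participants, a blinded researcher rates their presence and severity (as described for the dose review), and the adverse event summary carries no relatedness limit. No section says that the arms will be compared on the events sent to the HREC.

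A reader might also infer that serious events are withheld from the independent monitoring committee. The article says "An independent Data Monitoring Committee (DMC) will be formed and comprise experienced local, national and international members", and the Trial status section lets that committee and the HREC audit the trial at any time. What data the committee receives is commonly set out in a charter or the full protocol, neither of which is shown, so silence here is not exclusion.

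A third inference would be that an unblinded PI may stop the trial alone on data by arm. The Trial status section says "The HREC and PI, respectively, have the power to end the study early if the need arises", which does not describe such a decision, and this review asks for no change there.

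Finally, the full protocol may define adverse events more broadly. That would answer the visit-level part if it does, but it would not undo the restriction that the Ethics section states.

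**Conclusion.** The point holds in a limited form. An attribution step stands before both ethics notification and event collection. At the notification step no judge is named, the reporter knows the allocation, and nothing prevents the judgement from being made with that knowledge. The result is a gap in what ethics oversight is sure to see, and possible under-recording of events that participants do not attribute to treatment.

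The size cannot be estimated from the document. Any ratio of notified events between arms would only restate whatever proportions judged related one chose to assume, and it would describe notifications, not the planned summary. No bias in the safety analysis is shown.

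The conclusion rests on reading the Ethics rule and the visit question as they are worded, and on the absence of any other stated route for events that are not attributed. It is a low-cost improvement to safety reporting and does not put the primary result in doubt.

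**What to change.** - **Ethics section:** record and report every serious adverse event regardless of relatedness. Record any relatedness judgement as a separate item and name who makes it. Where feasible, that person should not know the arm and should not be the MADRS rater: the vortioxetine dose differs by arm and is hidden from raters, so a causality review could reveal the allocation to the person who scores the primary outcome.
- **Study schedule section:** ask at each visit for any adverse event, so that the summary in the Results analysis section covers all events and the terms match.

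The cost is a few more reports to the HREC, slightly more data entry, and a change to the wording of the visit question and the serious event form. If causality is to be judged blind, someone outside the rating team has to be found. For that reason this part is conditional on feasibility, whereas reporting regardless of relatedness is not.

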## Medications

### Celecoxib

Celecoxib, a cyclooxygenase 2 inhibitor, is a NSAID that has previously been used as an adjunct to antidepressant medication in the treatment of MDD in four trials, with three of these trials exploring six weeks of treatment at 400 mg daily [45–47] and one trial of eight weeks at 200 mg daily [48]. All four of these trials suggested improved antidepressant treatment effects for celecoxib add-on treatment, compared to antidepressants plus placebo. Recent meta-analyses associated celecoxib with an increased efficacy of antidepressant therapy [41]. In particular, augmentation of antidepressant medication with celecoxib showed an improved antidepressant effect by a standard mean difference (SMD) of 0.82 (95% confidence interval [CI]: 0.46–1.17) and without heterogeneity between the studies (I^2^ = 0%) [41]. Furthermore, remission of depression was improved by an odds ratio (OR) of 7.89 (95% CI: 2.94–21.17) and treatment response by an OR of 6.59 (95% CI: 2.24–19.42) by this 6–8-week add-on treatment hence the choice of celecoxib 400 mg for our study. Finally, one trial included peripheral blood tests and found that higher levels of the pro-inflammatory marker IL-6 predicted better antidepressant response to the celecoxib add-on [45]. In the present study, celecoxib 400 mg or placebo is given daily to all the participants at a constant dosage from baseline to week 6.

### Vortioxetine

Vortioxetine has been chosen as it has a TGA indication in Australia for the treatment of MDD. The Royal Australian and New Zealand College of Psychiatrists (RANZCP) guidelines for the treatment of MDD include use of antidepressant medication such as vortioxetine. The RANZCP guidelines state vortioxetine is most likely to be useful in melancholia and severe depression [39]. Furthermore, vortioxetine is the only antidepressant listed in the RANZCP guidelines that is likely to be useful in enhancing the remittance of cognitive symptoms of depression [39], since it has been demonstrated to have beneficial effects on the cognitive symptoms seen in MDD [40].

All the study medication will be provided for free over the entire RCT and post-RCT periods, for eight months in total.

## Clinical, self-report and cognitive assessment

When not self-administered, the following clinical and cognitive assessment are administered by a clinician researcher who is blind to whether participants receive celecoxib or placebo. The administering researcher has been trained in all clinician-rated scales. These scales have been referred to as ‘clinician-administered questionnaire’ in the text. A summary of all scales used in the study can be found in Table 2 (see Table 2). The table lists whether the rater is a study clinician who is blinded to anti-inflammatory or placebo medication status and baseline CRP level, or self-administered. While many scales are self-administered, they are all completed under the supervision of research personnel who can offer clarification if required.

**Table 2 Tab2:** Table summarising all clinician-administered and self-administered scales used in the study. Study scales used in the anti-inflammatory treatment of depression study, their range, cutoff for study eligibility and rater identity

Scale name	Purpose of scale	Score range	Study cutoff	Rater
Montgomery–Åsberg Depression Rating Scale (MADRS)	Detect the presence and severity of depressive symptoms	0–60 (0–6 = normal/recovered; 7–19 = mild depression; 20–34 = moderate depression; and 35–60 = severe depression)	≥ 26, or if Item 10’s (suicidal ideation) score ≥ 5	Blinded study clinician
Mini-International Neuropsychiatric Interview (MINI)	Fulfilment or non-fulfilment of minimum diagnostic criteria for Axis I neuropsychiatric disorders and antisocial personality disorder	N/A	Any current psychotic disorder	Blinded study clinician
Columbia-Suicide Severity Rating Scale (C-SSRS)	Relative severity of suicidal ideation and behaviour in the last month and lifetime	0–33, where the higher the number, the greater the severity of ideation and likelihood of suicidal behaviour	N/A	Blinded study clinician
National Adult Reading Test (NART)	Predictor of IQ, independent of psychiatric morbidity	0–50, with higher scores correlated with higher IQs	N/A	Blinded study clinician
Clinical Global Impression scale (CGI)	Allows for quantification of patient morbidity (CGI-S), and progress and treatment response over time (CGI-I)	2 scales of 0–7; in CGI-S, 0 is normal while 7 indicates complete disability; and in CGI-I, 0 indicates substantial improvement while 7 indicates severe exacerbation of symptoms	N/A	Blinded study clinician
Functioning Assessment Short Test (FAST)	The extent of difficulty the participant has had in specific areas of everyday life in the specified timeframe	0–72, where the higher the number, the more severe the difficulty in functioning	N/A	Blinded study clinician
WHO-5 Well-Being Index	Estimates the participant’s well-being by gauging the proportion of time spent in a positive state of mind in the last 2 weeks	0–100, where the higher the number, the greater the participant’s well-being	N/A	Self-administered
Endicott Work Productivity Scale (EWPS)	Assessment of productivity when at work and record of hours worked	0–100, where the higher the number, the poorer the participant’s productivity at work	N/A	Self-administered
Work Limitation Questionnaire (WLQ-25)	Assessment of impairment to full functional capacity at work	0–100, where the higher the number, the less able the participant is to meet the requirements of their work	N/A	Self-administered
Sheehan Disability Scale (SDS)	The degree to which the participant has been impaired in work/school, social and family life due to disability	3 scales from 0 to 10, considered independently or combined; and count of days unable to work or unproductive	N/A	Self-administered
THINC-it® Perceived Deficits Questionnaire-5-D (PDQ-5-D)	Participant’s own recollection of cognitive difficulties in the past 7 days	0–20, where the higher the number, the greater the perceived cognitive deficit; score can also be multiplied by 200 to give the same scoring range as the subsequent THINCit® tests	N/A	Self-administered
THINC-it® Spotter	Test of attention and response speed	Overall score: 0–4000, where a higher number indicates greater ability in all measures; additionally, accuracy (range: 0–40) and speed (mean response time) are recorded	N/A	Self-administered
THINC-it® Symbol Check	Test of working memory and attention	Overall score: 0–4000, where a higher number indicates greater ability in all measures; additionally, accuracy (count correct vs incorrect) and speed (mean response time) are recorded	N/A	Self-administered
THINC-it® Codebreaker	Test of attention, perceptual speed, motor speed, visual scanning and memory	Overall score: 0–4000, where a higher number indicates greater ability in all measures; additionally, accuracy (count correct vs incorrect) and speed (mean response time, maximum 1 s) are recorded	N/A	Self-administered
THINC-it® Trails	Test of visual search speed, scanning, speed of processing, mental flexibility and executive functioning	Overall score: 0–4000, where a higher number indicates greater ability in all measures; additionally, accuracy (count correct vs incorrect, error type) and speed (total completion time) are recorded	N/A	Self-administered

